#### Randomisation and enrolment

The randomisation list will be computer-generated by an independent statistician. A stratified block permuted randomisation will be used with the Kellgren–Lawrence grading scale (grade 0–2 vs. grade 3–4) as the stratification variable [24]. The block size will not be disclosed, to ensure concealment. Randomisation will be enabled through a secure, web-based application.

The surgeons performing the operation will be assigned to an operation type according to their expertise. Each surgeon will perform a single operation type and each operation type will be conducted by three surgeons.

A patient will be managed by one of the three surgeons corresponding to the treatment group the patient is randomly assigned to. It is anticipated that each surgeon will treat roughly the same number of patients.

The study will enrol a total of 243 patients to be treated by nine orthopaedic surgeons at Western Health; this accounts for approximately 81 patients per operation type.

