#### Sample size

Sample size is computed on the basis of our primary hypothesis that at least one of the three surgical methods will be superior to one other surgical method for total hip replacement, as measured by the change from pre-operation to 24 months post-procedure in the overall Oxford Hip Score. The minimal clinically important difference is at least five points and the best estimate for the standard deviation is nine points [25–28]. To control for the Type I error rate due to three treatment comparisons, a Holm–Bonferroni multiplicity adjustment will be used (i.e., a two-sided significance level of 0.0167 instead of 0.05). Using a two-sample *t* test, this leads to a sample size of 70 patients per operation type to obtain 80% power. This sample size needs to be increased because of two factors. Each surgeon will only perform one surgical method and as a result each patient cannot be assumed to generate independent observations because patients are clustered by surgeon. As a result, the sample size is inflated by 2.2% (i.e., a factor [1 + (*m* − 1) × intracluster correlation coefficient]) to achieve the variance that would have been anticipated had there been no clustering, assuming that each surgeon will treat 23 (*m* = 23) patients and the intracluster correlation coefficient is 0.001 [29, 30]. In addition, a drop-out rate of 10%, which includes a mortality of 2%, is anticipated at 24 months post-procedure [31], leading to an additional 11.1% increase in sample size.

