#### Data analysis

Baseline data consisting of demographic data (e.g., age, sex, diabetes, smoking status), medical history and the Kellgren–Lawrence grading will be summarised by operation type and overall and baseline imbalances will be explored.

The analysis of Oxford Hip Score and visual analogue scale will adopt the intention-to-treat approach, analysing all patients according to their randomly assigned operation type. The primary parameter Oxford Hip Score assesses 12 items on symptoms and functional status; the sum of the scores for the 12 items yields an overall score with range 0 to 48, where higher overall Oxford Hip Scores represent better outcomes.

The change from pre-operation to post-procedure in overall Oxford Hip Score will be analysed using a mixed-model repeated measures analysis, including as fixed in the model the categorical effects operation type, visit and operation type by visit interaction, and the stratification factor Kellgren–Lawrence grade, as well as the fixed continuous covariates pre-operation overall Oxford Hip Score and pre-operation overall Oxford Hip Score by visit interaction.To account for repeated measurements within a patient, an unstructured (co)variance structure will be used to model within-patient errors, whereby a patient is nested by surgeon.To account for potential clustering of the outcome due to a single surgeon using only one operation type, robust standard errors will be used. This primary model will include all patients with a pre-operation and at least one post-procedure overall Oxford Hip Score.

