The primary hypothesis will be examined by three contrasts evaluating the change from pre-operation to 24 months post-procedure in overall Oxford Hip Score for the posterior versus Hardinge approach, the posterior versus anterior approach, and the Hardinge versus anterior approach using an alpha level of 1.67% for each contrast to allow for the three comparisons. The primary hypothesis will be rejected if at least one of the three comparisons reaches statistical significance using the two-sided Holm–Bonferroni-adjusted alpha level. An estimate and corresponding two-sided multiplicity-adjusted 98.33% confidence interval will be provided for each comparison. This analysis method uses a model-based approach to handle missing data providing valid inference if the missing data mechanism is ignorable (i.e., missing completely at random or missing at random). A range of sensitivity analyses to examine the robustness of the primary model results will be performed to explore the impact of the results of different missing data techniques under the same and under different missingness assumptions.

The primary model will be extended to include potential confounders, such as age, sex, diabetes or smoking status, to obtain adjusted treatment effect estimates. To investigate whether there is a different treatment effect between the subgroups defined by the Kellgren–Lawrence grade, appropriate interaction tests will be performed. The key secondary parameter measuring self-reported pain will be measured using a visual analogue scale with range 0 to 100%, where lower values represent a better outcome, and will be analysed similarly to the primary parameter.

Complications will be reported for all randomised patients who had their surgery according to the operation type they actually received. The number and percentage of patients with dislocation, infection, intraoperative and periprosthetic fractures during the entire post-procedure trial period will be reported by operation type and operation types will be compared using a modified Poisson model within the model operation type and the subgroups defined by the Kellgren–Lawrence grade whilst accounting for clustering by surgeon via robust standard errors. Residual regional pain measured using a visual analogue scale will be investigated similarly to the key secondary parameter. A two-sided alpha level of 5% will be used throughout, except for the primary parameter.

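### The primary Oxford Hip Score model leaves out age, sex and BMI, which the trial collects; adding them would give a small, nearly free gain in precision

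*Protocol article*

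**What the plan says.** In the protocol article, Data analysis, the mixed model for repeated measures has as fixed effects "the categorical effects operation type, visit and operation type by visit interaction, and the stratification factor Kellgren–Lawrence grade", together with the "fixed continuous covariates pre-operation overall Oxford Hip Score and pre-operation overall Oxford Hip Score by visit interaction". The three contrasts at 24 months that decide the trial come from this model, each tested at 1.67%. Its standard errors are robust, to allow for clustering by surgeon.

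Age and sex are collected: the same section lists "Baseline data consisting of demographic data (e.g., age, sex, diabetes, smoking status), medical history and the Kellgren–Lawrence grading". BMI is on the list of case report forms under Measurement tools.

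Further covariates enter a second model: "The primary model will be extended to include potential confounders, such as age, sex, diabetes or smoking status, to obtain adjusted treatment effect estimates". BMI is not among the examples. The pain visual analogue scale is to be analysed in the same way as the primary parameter, so it has the same covariate set.

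On surgeons, Randomisation and enrolment says "A patient will be managed by one of the three surgeons corresponding to the treatment group the patient is randomly assigned to" and "It is anticipated that each surgeon will treat roughly the same number of patients". Sample size assumes that "the intracluster correlation coefficient is 0.001".

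**The concern.** The plan itself treats age and sex as variables likely to relate to outcome, but keeps them out of the one model on which the primary hypothesis is decided. Baseline covariates that predict the 24-month score reduce the residual variance. They therefore narrow the interval and raise power without recruiting another patient. The design aims for only 80% power per contrast at a 1.67% level and adds almost nothing for surgeon variance, so even a small gain is useful.

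A second consideration comes from the clustered standard error. If older or heavier patients tend to go to particular surgeons within an arm, an unadjusted model leaves that pattern in the surgeon-level residuals, and the robust standard error picks it up. With the covariates in the model, most of it is removed.

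**Working it through.** **Inputs from the protocol article.** Difference 5 points, SD 9, two-sided alpha 0.0167 (0.05/3), 80% power, 70 per arm before inflation, intracluster correlation 0.001 with 23 patients per surgeon, 10% drop-out (all Sample size); 243 patients, about 81 per arm, nine surgeons (Randomisation and enrolment).

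**Reproducing the plan's figure.** For a two-sample t test with n per arm:

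- standard error = 9 × √(2/70) = 1.521
- noncentrality = 5 / 1.521 = 3.287
- critical value t(138) at 0.05/3 two-sided = 2.424
- power from the noncentral t = 80.5% (79.8% at 69 per arm)

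So 70 per arm is right. Inflation gives 70 × [1 + 22 × 0.001] / 0.90 = 79.5, or 80 per arm. The stated 81 is close to this and equals three surgeons × 27.

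**Effect of the covariates.** Let R² be the share of residual variance at 24 months explained by age, sex and BMI together. The documents give no value, so 2%, 5% and 10% are assumed. The adjusted SD is 9 × √(1 − R²).

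| Assumed R² | SD | Standard error of contrast | Noncentrality | Power at 70 per arm | Patients per arm it is worth (70 × R²) |
|---|---|---|---|---|---|
| 0 | 9.00 | 1.521 | 3.287 | 80.5% | – |
| 2% | 8.91 | 1.506 | 3.320 | 81.4% | 1.4 |
| 5% | 8.77 | 1.483 | 3.372 | 82.7% | 3.5 |
| 10% | 8.54 | 1.443 | 3.464 | 85.0% | 7.0 |

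Taking three degrees of freedom off the 138 changes these powers by less than 0.1 percentage point.

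**Does patient mix between surgeons add error?** A simulation used nine surgeons, three per arm, with 24 evaluable patients each. Patients were randomised to arm and then sorted to differing degrees among that arm's surgeons by a prognostic index explaining 10% of the variance (8,000 runs per setting).

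| Share of index variance lying between surgeons | True SD of contrast, unadjusted | Clustered robust SE, unadjusted | True SD, adjusted | Clustered robust SE, adjusted |
|---|---|---|---|---|
| 0.03 (random) | 1.52 | 1.32 | 1.45 | 1.27 |
| 0.10 | 1.51 | 1.48 | 1.44 | 1.25 |
| 0.18 | 1.49 | 1.64 | 1.42 | 1.24 |
| 0.41 | 1.51 | 2.02 | 1.45 | 1.23 |

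Three results follow.

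1. The true error of the unadjusted contrast stays flat however patients are sorted, because sorting within an arm changes neither who is in the arm nor the arm mean.
2. The reported clustered standard error grows with sorting if the model is unadjusted, and stays level if it is adjusted.
3. The adjusted robust standard error remains below the true SD (about 1.23 to 1.27 against about 1.44). Rejection under the null with normal critical values was 10% to 11% against a nominal 1.67%. That is a problem of having nine clusters, and covariates do not touch it.

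**The case against.** The strongest reply is that nothing here is an error. In a randomised comparison, leaving out prognostic covariates is a choice about efficiency. The model already has the pre-operation score, its interaction with visit and the stratification factor. A covariate-adjusted analysis naming age and sex is already planned, and its open wording does not exclude BMI. The gain rests on an R² that the documents do not give. All of this stands, and it is why the point is a modest suggestion. It does not remove the point, because the primary model is specified term by term in the text shown and the adjusted analysis does not decide the trial.

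Three stronger readings are tempting, and the documents do not support them.

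- A reader might infer that differing patient mix among an arm's three surgeons adds error to every contrast and so erodes the planned power. It does not: patients are randomised to arm, and the true SD of the contrast is unchanged. Only the reported clustered standard error can widen. Power losses computed by treating patient mix as an added surgeon effect therefore do not describe true error.
- A reader might infer that patients are not allocated to surgeons in any controlled way. The article states no rule, but a condensed article may leave this to the full protocol. Silence is not evidence of free choice, and equal numbers are anticipated.
- A reader might infer that the extended model's list will be chosen from the imbalances seen. The statement that "baseline imbalances will be explored" belongs to the descriptive baseline summary, and the text does not make the extended model depend on it. The final list may also be fixed in an analysis plan that is not shown.

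**Conclusion.** The point holds as a small efficiency loss in the deciding analysis. It is not a bias and not a fault in the validity of the trial. Power per contrast at 70 per arm would rise from 80.5% to 81.4%, 82.7% or 85.0%, worth 1.4, 3.5 or 7 patients per arm, if age, sex and BMI explain 2%, 5% or 10% of the residual variance. Those shares are assumptions. So is the use of SD 9 as the residual SD of the primary model, since the article does not say whether 9 already reflects adjustment for the pre-operation score. A secondary benefit is that adjustment keeps differences in patient mix between surgeons out of the clustered standard error; its size depends on a degree of sorting that the documents do not give. The downward bias of robust standard errors with nine surgeons remains and is a separate matter.

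**What to change.** In the specification of the primary Oxford Hip Score model, add age (continuous), sex and BMI (continuous) as fixed covariates. Make the same change to the pain-scale model, which follows the primary one. Fix this in writing before any outcome data by arm are seen.

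The cost is a change of wording and three degrees of freedom. All three variables are already collected, so there is no new data collection and no change to recruitment or conduct. Patients with a missing covariate should not be lost from the primary analysis, so the analysis plan should say how a missing BMI is handled.

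The change should not be presented as a remedy for clustering with nine surgeons. That needs its own correction to the standard errors and reference distribution.

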### Statistical considerations

The null hypothesis for this study is that patient-reported outcomes following three different approaches for total hip arthroplasty are no different when directly compared 24 months post-procedure. In addition we hypothesise that complication rates are the same between approaches. There is no randomised controlled trial that directly compares these three approaches for total hip arthroplasty. We are hence designing our study as a superiority study, looking for a significant difference in Oxford Hip Score and visual analogue scale rating between the different trial arms.

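### The planned robust Poisson comparison of complications gives a meaningless p-value if an arm has no events, and the protocol names no rule for that case

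*Protocol article*

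**What the plan says.** All on this point is in the protocol article.

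- **Hypothesis** (Statistical considerations): "In addition we hypothesise that complication rates are the same between approaches".
- **Outcomes** (Data analysis): "The number and percentage of patients with dislocation, infection, intraoperative and periprosthetic fractures during the entire post-procedure trial period will be reported by operation type".
- **Model** (Data analysis): "operation types will be compared using a modified Poisson model within the model operation type"; Kellgren–Lawrence group is the other model term.
- **Variance** (Data analysis): the model is to be fitted "whilst accounting for clustering by surgeon via robust standard errors".
- **Analysis set** (Data analysis): "Complications will be reported for all randomised patients who had their surgery according to the operation type they actually received".
- **Significance level** (Data analysis): "A two-sided alpha level of 5% will be used throughout, except for the primary parameter".
- **Size** (Randomisation and enrolment): nine surgeons, three per operation type, each doing one type only; for the 243 patients, "this accounts for approximately 81 patients per operation type".

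The document gives no expected complication rate. It names no alternative analysis for an arm with zero or very few events.

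**The concern.** Modified Poisson regression estimates risk ratios on the log scale. If an arm has no events, its estimated risk is zero and the log risk ratio is minus infinity. The software stops iterating when its convergence criterion is met, so the printed coefficient is arbitrary. A model-based standard error would become huge at that point and show that the data hold no usable information about the ratio. The robust standard error does not grow. Dividing a large arbitrary coefficient by an ordinary standard error gives an enormous Wald statistic.

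The trial is meant to inform the choice of surgical approach. Applied in the usual way, the stated method could report one approach as significantly safer for a complication on the strength of 0 versus 1 or 2 events.

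**Working it through.** **Inputs.** From the protocol article: 81 patients per arm; nine surgeons, three per arm, taken as 81/3 = 27 patients each; robust errors clustered by surgeon; two-sided 5%. Complication rates are assumed, because none is given.

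**The plan's own figure.** The Sample size section starts from 70 per arm for a 5-point difference, SD 9, two-sided alpha 0.0167 and 80% power. The noncentral t gives power 0.805 at 70, so this reproduces. Then 70 × 1.022 / 0.9 = 79.5, or 80. The stated 81 equals 27 × 3 and is close enough. Nothing here turns on the difference.

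**Step 1: why the robust standard error stays small.** Take 2 events in arm A (under two different surgeons), 0 in arm B and 1 in arm C, with operation type only in the model. An arm contributes to the variance of the log risk ratio the sum over its surgeons of (observed − fitted events)², divided by (fitted events in the arm)².

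- Arm A: fitted 2/3 per surgeon, residuals 1/3, 1/3 and −2/3. Contribution (1/9 + 1/9 + 4/9) / 2² = 0.167.
- Arm B: every patient has the same fitted value μ, so each surgeon's residual is −27μ. Contribution 3 × (27μ)² / (81μ)² = 1/3. The μ cancels, so this stays at 1/3 however close to zero the fitted risk goes.
- Sum 0.167 + 0.333 = 0.500. With the common finite-sample factor (9/8) × (242/240), the SE is √(0.500 × 1.134) = 0.753.

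The model-based variance from arm B is instead 1/(81μ), which grows without limit as μ goes to zero.

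**Step 2: refit.** The Poisson model with a surgeon-clustered sandwich variance, arm B versus arm A:

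| Events A vs B (of 81) | log RR | Robust SE | Robust Wald p | Model-based p | Fisher p |
|---|---|---|---|---|---|
| 2 vs 0, different surgeons | −20.4 | 0.753 | 2e-161 | 0.999 | 0.50 |
| 2 vs 0, same surgeon | −20.4 | 1.065 | 1e-81 | 0.999 | 0.50 |
| 1 vs 0 | −20.1 | 1.065 | 2e-79 | 0.999 | 1.0 |

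In the first row, tightening the convergence tolerance from 1e-3 to 1e-10 moves the coefficient from −9.4 to −25.4 and p from 1e-35 to 4e-249, with the SE fixed at 0.753. The p-value therefore reflects a software setting. If the zero arm is the reference level, the robust SE can instead come out undefined or unstable.

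**Step 3: how often an arm has no events.** For true rate p, q = (1 − p)^81 per arm, and the chance of at least one zero arm of three is 1 − (1 − q)³.

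| Assumed rate | q | At least one zero arm, one complication | Same, at least one of three independent complications |
|---|---|---|---|
| 1% | 0.443 | 83% | 99.5% |
| 2% | 0.195 | 48% | 86% |
| 3% | 0.085 | 23% | 55% |
| 5% | 0.016 | 5% | 13% |

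**Step 4: false positives under equal rates.** These are 1,000 simulated trials per rate with independent patients, Kellgren–Lawrence group in the model and pairwise Wald tests at 5%. Contrasts with one zero arm were significant in 97%, 95%, 94% and 97% of cases at 1%, 2%, 3% and 5%. At least one false pairwise result per complication occurred in 73%, 45%, 29% and 27% of trials. Contrasts with no zero arm rejected in 0%, 0.9%, 3.7% and 10.3%. At 5%, then, most of the 27% does not come from zero arms, which occur in only about 5% of trials.

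**The case against.** The strongest reply is that a sparse-data fallback is ordinary SAP content, the SAP is not shown, and the protocol names a model and a variance but no test statistic. A surgeon-clustered score test (two degrees of freedom, operation type only) rejected in under 1% of 1,000 simulated null trials at each of 1%, 2%, 3% and 5%. The stated model can therefore be tested safely. This stands in part: a fallback may exist elsewhere. But the protocol fixes a model with robust standard errors, whose standard output is the Wald test, and choosing the score test would itself be the rule that is not stated.

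Complications are also secondary, counts and percentages appear beside the model result, and a log risk ratio near −20 would alert a careful analyst. That limits the harm, but it leaves the remedy to be chosen after the data are seen.

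A reader might infer more than the document supports:

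- *That an event-free Kellgren–Lawrence stratum distorts the comparison of approaches in the same way, so that term should go.* It affects that term's own coefficient. With 3/2/3 events and none in one stratum, the 2-versus-3 contrast was −0.4055 with the term (SE 0.436) and −0.4055 without it (SE 0.435). The document does not say that either stratum is small.
- *That zero arms explain the whole false-positive rate.* At a 5% rate the excess comes mainly from three unadjusted contrasts and nine clusters.
- *That the plan will read non-significance as equal rates.* It states equality as a hypothesis within a superiority design and nowhere says this.
- *That a composite complication endpoint is needed.* That would be a redesign, and this problem does not require it.

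**Conclusion.** The point holds as a correction to a secondary-outcome analysis. The stated method, tested in the usual way, gives an invalid result whenever an arm has no events. This mechanism follows from the algebra and does not depend on the simulation. The exact p-value depends on software, tolerance and how events fall across surgeons; in the refits at default tolerance it was between about 1e-79 and 1e-161 where Fisher's test gave 0.50 or 1.0.

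How probable the situation is rests wholly on assumed rates. For a single complication a zero arm is about an even chance at 2% (48%), more likely than not at 1% (83%), and uncommon at 5% (5%). The primary Oxford Hip Score analysis is untouched, so this falls short of a must-fix.

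**What to change.** Add a short sparse-data rule to the complications paragraph, before any outcome data are compared by arm:

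- When any arm has zero or very few events (threshold fixed in advance), the robust Wald comparison from the Poisson model is not used. Report counts and percentages with exact or score intervals for the three pairwise risk differences.
- If a test is wanted in that case, name one: an exact test, a Firth-penalised model or a cluster-robust score test.
- Otherwise keep the modified Poisson model as planned, including the Kellgren–Lawrence term, with a small-sample correction for nine surgeon clusters.

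The change is to wording only; sample size and data collection stay the same. The price is statistical. Exact tests are conservative (in the null simulations Fisher's test rejected between 0% and 1.1% of contrasts) and do not model surgeon clustering, which the plan set out to handle. The score test keeps the clustering.
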